**Fig 1 pone.0330393.g001:**
[figure not shown]
Flow diagram of the inclusion process (TREND Statement).

### Eligibility criteria

Patients will be eligible for inclusion if they have a diagnosis of type 2 diabetes mellitus, are 18 years of age or older and have minimal physical fitness. This is defined as the ability to sit down and stand up from a chair without assistance, walk short distances independently (at least 100 meters), and perform light household tasks—such as making the bed, washing dishes, or preparing simple meals—without difficulty. This information will be collected through clinical observation and self-report by the participant during the initial interview.

Patients with medical contraindications, pregnant women, individuals who have recently undergone major surgical interventions that limit functional mobility, or who, according to clinical judgment, have not achieved sufficient recovery, will be excluded. Patients undergoing cancer treatment or who have completed such treatment within the past year will also be excluded, as the side effects, in addition to the symptoms of the disease, may persist for months or even years [27,28]. Finally, individuals with cognitive impairment will be excluded, as cognitive symptoms can appear in early stages and affect the ability to participate in the intervention, [29–31], as well as those diagnosed with dementia or severe cognitive or psychiatric disorders.

### Group allocation and masking

The distribution in the CG or IG will be performed sequentially in a 1:1 ratio in order of access to the study, i.e., the first patient who accepts the informed consent will be included in the IG, the next in the CG and so on until the sample is complete. This sequential assignment does not constitute strict randomization, and concealment techniques will not be employed. While this methodology is appropriate for research in real clinical settings, it may carry a risk of selection bias. This risk is acknowledged and will be considered when interpreting the results.

Due to the nature of the intervention, both the participants and the nursing staff and collaborating personnel will be aware of the assigned groups.

Additionally, the principal investigator will be responsible for data collection and analysis; therefore, outcome assessor blinding will not be applied.

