**Design and methodology:**

Quasi-experimental controlled study, single-center, parallel, two-branch, with a 12-month follow-up. We plan to recruit up to a total of 169 participants, who will be assigned in a 1:1 ratio to a control group (who will receive e-mails) and an intervention group (who will receive face-to-face group and individual visits and telephone calls). The active intervention has a duration of 6 months and will be carried out by nursing professionals. The primary outcomes are sedentary time measured with the Sedentary Behavior Questionnaire (SBQ) and the use of accelerometers, and the state of motivation to change measured through the Transtheoretical Model of Physical Exercise Change Questionnaire (TMPECQ).

**Trial registration.** ClinicalTrials.gov (NCT06893146).

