#### Anthropometric data.

Anthropometric measurements of weight, height, waist-hip circumference are collected by healthcare personnel using calibrated instruments and clinical standard procedures. Weight is measured with shoes and without heavy clothing. Height and weight are used to measure Body Mass Index (BMI) with the standardized formula, BMI = weight (kg)/ height (m)^2^. Anthropometric measurements will be taken at each participant’s health center of correspondence.

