#### Clinical characteristics.

Blood pressure and blood parameters are collected. In the latter, the levels of glucose, glycosylated hemoglobin (HbA1c), homeostasis model assessment-insulin residence (HOMA-IR), total cholesterol, high-density lipoprotein cholesterol (HDL-c), low-density lipoprotein cholesterol (LDL-c), triglycerides (TG), aspartate aminotransferase (AST), alanine aminotransferase (ALT) and gamma-glutamyl transferase (GAG) are examined, triglycerides (TG), aspartate aminotransferase (AST), alanine aminotransferase (ALT) and gamma-glutamyl transferase (GGT), creatinine, urea, creatinine clearance, iron, ferritin, sodium, potassium and C-reactive protein (CRP).

Blood samples will be drawn after a fasting period of at least 8 hours (no food or beverage intake) at the corresponding health center. Handling and transport will be conducted in accordance with standardized quality protocols, and the samples will be processed and analyzed in an accredited laboratory, following the current regulations of the Community of La Rioja. Biochemical analyses will be performed using automated techniques, employing equipment that is periodically calibrated and validated.

In relation to blood pressure, measurements will be taken at the corresponding health center. Readings will be obtained over the brachial artery, after 5 minutes of rest while seated and with the arms resting at heart level. Long-sleeved shirts will be removed for a correct reading and the cuff size must be adequate.

Data related to diabetes disease (year of diagnosis, antidiabetic treatment currently used, associated complications and frequency of Health care), smoking, alcohol consumption, past injuries and major surgeries, sedentary lifestyle, motivation to change physical exercise, physical activity and quality of life will also be collected through medical history and self-report.

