#### Level of sedentary lifestyle.

The level of sedentary lifestyle will be measured with the use of accelerometers and a questionnaire validated in Spanish. The questionnaire used is the Spanish version of the SBQ (S4 Appendix). This instrument measures the time spent in sedentary behaviors from the time the person gets up to the time he/she goes to bed, both during the week and at weekends. The responses are provided on numerical scales, and then the total number of hours spent on each activity is summed. The interclass correlation is 0.83–0.86 and the reliability index of the questions varies from 0.52 to 0.96 [32].

In addition, sedentary time will be evaluated quantitatively using accelerometers. The model used in our study is the ActiTrainer, which is small (8.56 x 3.81 x 1.52 cm) and light (48 g), ensuring great comfort during use. Previous studies have supported its use for an objective and more reliable measurement of the effectiveness of interventions [33–38] They will be placed by the study nurse during the measurement periods (T0-3), however, both the participants of the CG and the IG will receive training on their proper placement, removal and protocol. These should be worn at the waist, fastened with a well-fitting elastic belt, placed in the morning and removed at bedtime and during periods of exposure to water (bath, shower, swimming, etc.). To avoid skin irritation in case of incorrect fit, they may be worn over clothing. Participants must wear the device for 5 consecutive days, with a minimum of 10 waking hours per day.

This device only detects human movement, electronically filtering high-frequency vibrations produced by cars, buses, trains, etc. It has no other function than to measure physical activity through an encryption of internal operations that require specific software and cannot be used for any other purpose. It does not emit radiation or interfere with the human body. However, any eventuality must be reported.

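### The reason given for waiving all assessor blinding does not cover waist-hip and blood pressure readings taken at participants' own health centres

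*Protocol article*

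**What the plan says.** The section Group allocation and masking makes two statements. The first, attributed to the nature of the intervention, is that "both the participants and the nursing staff and collaborating personnel will be aware of the assigned groups". The second is that "the principal investigator will be responsible for data collection and analysis; therefore, outcome assessor blinding will not be applied". The waiver is general and exempts no outcome.

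The measurement sections describe who takes the readings and where:

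- Anthropometric data: "Anthropometric measurements of weight, height, waist-hip circumference are collected by healthcare personnel using calibrated instruments and clinical standard procedures", and "Anthropometric measurements will be taken at each participant’s health center of correspondence".
- Clinical characteristics: "In relation to blood pressure, measurements will be taken at the corresponding health center". The person taking the reading is not named. Blood is also drawn at the health centre, and "the samples will be processed and analyzed in an accredited laboratory" by automated techniques.
- Level of sedentary lifestyle: the study nurse fits the accelerometers.

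The Abstract states: "The primary outcomes are sedentary time measured with the Sedentary Behavior Questionnaire (SBQ) and the use of accelerometers", together with the motivation questionnaire (TMPECQ). The Discussion lists the lack of blinding of participants and researchers as a limitation and describes no step to reduce it.

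**The concern.** The waiver is presented as following from the principal investigator's role. That reasoning works only where the principal investigator, or someone who necessarily knows the arm, takes the measurement. The article sends part of the measurement elsewhere, to staff who have no described role in the intervention.

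Waist and hip circumference vary with tape position and tension, and blood pressure with repeat readings and rounding. A measurer who knows the arm can move such readings in the expected direction without intending to. Allocation is alternating and unconcealed, so measurement is one of the few places left where this design can guard against bias. The readings also matter to the study question: the Objective and the Objectives section both ask whether less sedentary time improves clinical and anthropometric parameters.

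**Working it through.** The plan gives no figure on this point, so the check is mainly a comparison of sections.

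**1. Does the stated reason reach each outcome?**

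| Outcome | Who measures, and where | Covered by the reason given? |
|---|---|---|
| SBQ, TMPECQ (primary) | Participant, self-report | Masking is not possible, because the participant knows the arm |
| Accelerometer sedentary time (primary) | Fitted by the study nurse | The fitter knows the arm |
| Data handling and analysis | Principal investigator | Yes |
| Weight, height, waist-hip | Healthcare personnel, own health centre | No |
| Blood pressure | Own health centre, person not named | Not shown |
| Blood chemistry | Drawn at health centre, automated laboratory analysis | Not shown, but little exposed |

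**2. Do health-centre staff deliver the intervention?** Study design has the research nurse direct the interventions. Study activities assigns the calls to a trained nurse with a diabetes nurse educator, and the individual visit to the study nurse. The Abstract speaks only generally of nursing professionals. No section gives health-centre staff a role.

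**3. Does the other reason fill the gap?** The nature of the intervention explains why participants and those who deliver it know the arm. It does not explain why a person holding a tape or cuff at a separate site must know. If these staff count among the collaborating personnel, they are unmasked without a stated need. If they do not, the general waiver is wider than it has to be. The section needs rewording in either case.

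**4. Which readings matter?** Weight is taken on calibrated instruments and laboratory values are automated, so both leave the operator little room. That leaves mainly waist-hip and blood pressure.

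**5. What could a shift do? (Illustration only.)** The documents give no size for a measurement shift, so it is assumed here as b, in SD units, in one arm. With n per arm, no true effect and a two-sided 0.05 test:

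false-positive rate = 1 − Φ(1.96 − b/√(2/n)) + Φ(−1.96 − b/√(2/n))

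The plan assigns 84 and 85 participants, so n = 84 and √(2/84) = 0.154. After the planned 15% dropout, 169 × 0.85 ≈ 144, or 72 per arm, and √(2/72) = 0.167.

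| Assumed shift b | 84 per arm | 72 per arm |
|---|---|---|
| 0.1 SD | 9.9% | 9.2% |
| 0.2 SD | 25.4% | 22.4% |
| 0.3 SD | 49.4% | 43.7% |

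These rates are for a single unadjusted two-group comparison. The planned Bonferroni correction would lower them by an amount that depends on the number of comparisons, which the article does not give. Masking changes neither the sample size nor the significance level.

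**The case against.** Several points on the other side stand.

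- Being responsible for data collection is compatible with other people taking the readings. A reader might call the sections contradictory, but the text supports less than that: the reason is too narrow for the waiver built on it.
- A reader might infer that health-centre staff will know the arm and will bias the readings. The article does not say that they are told, and it does not say who takes blood pressure. The exposure is possible, not established.
- The article specifies rest, posture, arm position and cuff size for blood pressure, and calibrated instruments with standard procedures for anthropometry. This narrows the room for bias but does not remove it.
- Masking would be fragile. Participants know their group and could reveal it at their own health centre.
- The lack of blinding is disclosed openly, and the Discussion calls it common in behavioural studies. It does not claim that it is unavoidable. Disclosure is to the authors' credit, but it does not replace a protection that is available for some of the readings.

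None of this supplies a reason for leaving these particular measurers unmasked.

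**Conclusion.** The point holds as a limited one. The principal investigator's role does not justify a general waiver that includes anthropometry and blood pressure taken at participants' health centres. The readings affected are secondary, mainly waist-hip and blood pressure, at the planned measurement times (T0 to T3) in up to 169 participants. The conclusion assumes that health-centre staff have no part in the intervention, which is how the article reads but is not stated outright.

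The size of any bias is unknown, and the rates under the assumed shifts are not estimates for this trial. A reader might infer that the main result is at risk through this route, or that masking these staff would protect it. The documents do not support that: the primary outcomes are two self-report questionnaires and an accelerometer fitted by the study nurse, and masking at the health centres protects none of them. Nor should the waiver sentence simply be deleted, because it truthfully discloses that an unblinded principal investigator collects and analyses the data.

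**What to change.** In Group allocation and masking:

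1. Limit the waiver to the self-reported outcomes, accelerometer fitting by the study nurse, and the principal investigator's own data collection and analysis. Keep the disclosure that the principal investigator is unblinded.
2. State that health-centre staff who take anthropometry and blood pressure are not told the allocation, and that any paperwork sent to them carries only the study code.
3. State that participants are asked not to mention their group at measurement visits.

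In Clinical characteristics, say who takes blood pressure. In the Discussion, keep the limitation and add that masking of these readings is partial, because some participants will reveal their group.

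The cost is low but not nil: revised wording, a short instruction to the health centres and one to participants. Staff, visits and sample size stay the same.

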### Study activities

The study has a total duration of 12 months. The intervention period is developed during the first 6 months. The flow diagram of the planned study procedure is detailed in Fig 2.

**Fig 2 pone.0330393.g002:**
[figure not shown]
Flow chart of the planned study procedure.

The CG will receive every two months detailed written information on healthy lifestyle habits by e-mail, emphasizing the importance of maintaining an active lifestyle, and will also be provided with standard educational material on the management of type 2 diabetes; this group will not receive additional interventions during the study period.

The IG will receive an intervention that will include two group sessions, bimonthly phone calls and a face-to-face visit with the study nurse.

The group sessions will be divided into two groups according to age, with a cutoff point at 65 years, and each subgroup will have the meeting on a different day, the first one will be held in the first month and the second one in the fifth month. This division will be implemented solely to facilitate the organization and convenience of the participants; both subgroups will receive the same content and duration in the sessions. The division does not imply any differences in the intervention but aims to optimize group dynamics; therefore, no differential effects are expected between the age subgroups.

The first session will focus on providing information about diabetes and sedentary behavior, explaining the health risks associated with sedentary habits as well as the benefits of adopting healthier lifestyles. Additionally, it will seek to empower participants to make informed decisions regarding their health.

The second session will be oriented towards reinforcing and consolidating the habits acquired, with an emphasis on identifying strategies for long-term maintenance, establishing sustainable routines, and preventing relapse. Each group meeting will have an approximate duration of 60–90 minutes.

Phone calls will be made every two months using motivational interviewing techniques with the aim of educating on habits and behaviors that reduce sedentary lifestyles, addressing needs and concerns on an individual basis, and enhancing patients’ motivation, well-being and quality of life. The information will be self-reported and qualitative, aimed at supporting and adjusting the program according to the needs of each participant, rather than obtaining standardized quantitative measures.

The calls will last between 15 and 20 minutes. Participants will be informed that the sessions should conclude within this timeframe; however, calls may occasionally be extended if the 15-minute mark occurs at an inconvenient moment to end the conversation. Any topic related to diabetes management is open for discussion.

First call: It will be ensured that the patient understands the program instructions, initial impressions and difficulties will be explored, and early adherence to sedentary behavior change will be assessed.Second call: Progress in reducing sedentary time will be evaluated, and emerging barriers or issues will be considered. Additionally, motivation will be reinforced.Third call: The overall experience and achievement of objectives will be reviewed.

If no response is obtained, up to three call attempts will be made, repeated over three consecutive days. If contact is not established after this period, the call will be considered missed, and the next call will be scheduled for two months later.

The motivational telephone interviews will be conducted by a nurse with complementary training in diabetes and motivational communication, together with a diabetes nurse educator who contributes clinical experience and specific training in the management of this disease. Both professionals have received specific training on the study protocol and intervention script, thereby ensuring the uniformity, quality, and fidelity of the calls made to participants.

The same purpose is served by the face-to-face visit that will be conducted in the third month of the study (Fig 3). During this individual session with the study nurse, progress in reducing sedentary behavior will be reviewed, specific questions will be addressed, and personalized emotional and motivational support will be provided, with the aim of enhancing the participant’s perceived support in the self-care process. Additionally, the level of engagement with the program and the understanding of the proposed objectives may be directly assessed.

**Fig 3 pone.0330393.g003:**
[figure not shown]
Nursing interventions for the intervention group.

Measurements for all participants in the CG and the IG are taken at the beginning of the study (T0), at 3 months (T1), at an intermediate phase (6 months, T2) and at 12 months from the beginning of the study (T3). Once the 12 months have elapsed, the study will be terminated. By then, data collection will have been completed, and the results are expected to be available within the following 3 months.

### Ethical approval

The present study is approved by the Ethics Committee for Drug Research in La Rioja (Ref. CEImLAR PI 778) and will comply with all established ethical standards. Healthcare professionals participating in the study will sign a document in which they undertake to protect the confidentiality of all patients. Before any procedure is performed, free and voluntary written informed consent must be obtained from each patient, which may be voluntarily revoked at any time during the study.

The information obtained in the study will be confidential and stored in coded form in an automated data file. The guidelines established in the Declaration of Helsinki, the current ethical guidelines for research involving human subjects and the Data Protection Act and the legislation in force in Spain will be followed. The processing of personal data of all patients will comply with the provisions of the Organic Law 3/2018 of December 5, 2018, on the Protection of Personal Data and Guarantee of Digital Rights and the provisions of Regulation (EU) 2016/679 of the European Parliament and of the Council of 27 April 2016 on Data Protection (GDPR). Our study design respects fundamental ethical principles and protects the welfare and rights of all participants.

Monitoring, audits, CEImLAR reviews and regulatory inspections will be allowed with the study, providing direct access to the original data.

Ethical audits are expected to be conducted annually and at the conclusion of the study. The research team will notify the ethics committee of any substantial protocol modifications through a written report sent via email, for evaluation and approval prior to implementation.

In the event of significant changes affecting participants, these will be communicated directly to them, and their informed consent will be requested again if necessary.

### Measurements and evaluations

Data will be collected at baseline (T0), three months (T1), interim (6 months = T2) and 12 months (T3) from the start of the study.

#### Sociodemographic data.

Sociodemographic data will be collected on the participants, such as age, sex, place of residence, marital status, educational level, occupation, and employment status. They will be collected through the primary care clinical history and through a self-report that the participants will be asked to complete in the initial phase of the study (T0). These variables are documented in the S3 Appendix.

#### Anthropometric data.

Anthropometric measurements of weight, height, waist-hip circumference are collected by healthcare personnel using calibrated instruments and clinical standard procedures. Weight is measured with shoes and without heavy clothing. Height and weight are used to measure Body Mass Index (BMI) with the standardized formula, BMI = weight (kg)/ height (m)^2^. Anthropometric measurements will be taken at each participant’s health center of correspondence.

